### Gender differences

With respect to the research questions, we hypothesize that potential gender differences will be observed within the muscle synergies. We think that the exoskeleton use will reduce shoulder muscle activity significantly [e.g., (54)] but first studies suggest that women might have less muscle activation in the shoulder muscles while wearing an exoskeleton (33). On the other hand, with respect to the design and the weight of the exoskeleton, women potentially could use different movement patterns to manage the tasks (56) due to differences in biomechanical and anthropometric trunk muscle geometry of females and males (56, 57). We anticipate that women show more bending backwards movements including a higher compensatory muscle activation in the abdominal and neck muscles. However, this idea has to be proven within our experimental design.

Moreover, as women are merely not integrated into the iterative designing processes of exoskeletons, yet, we propose more discomfort and less usability in the ratings by the women. This discomfort especially will be reported for the shoulder region (41).

In line with the cognitive resource theories (36), this discomfort might lead to more attentional resources spending on the discomfort and less resources available for the working DT situation. This will increase the cognitive-motor interference especially in the DT situation and could be observed with more cortical activation in the prefrontal cortex [*cf.* (35)]. Moreover, the working accuracy will decrease (58).

### Fatigue effects

Regarding physical fatigue we suppose that firstly the overall gender effects might be reduced. One potential explanation lies in the idea that the additional required motor resources after fatigue will reduce the discomfort effect. According to fatigue it has to be assumed that the task management requires more muscle activity that can be reduced by the exoskeleton use (59). As this is relevant for both genders, the muscle activity and accompanying synergies might converge. Nevertheless, it is unclear if the weight of the exoskeleton affects muscle activity between men and women differently.

However, the organizing of body movement after fatigue needs more executive control in the motor cortex (60) and this will lead to less attentional resources available for the detailing recognition of the discomfort. This hypothesis will be proven by the analysis of the fNIRS data, regarding a potential shift from parietal to frontal cortex activation. This mechanism should be equal for male and female participants and might only be affected by age (61).

Moreover, as more resources for postural control and motor adjustments will be required after fatigue, the cognitive-motor interference in the DT condition will rise while movement accuracy will decrease. If the exoskeleton use will reduce this effect, it needs to be examined within our experimental design. On the other hand, the physical fatigue could also increase the proposed differences in upper body postures (more bending backwards of the women). This hypothesis would lead to increased muscle activity in the supporting muscles and might change muscle synergy patterns.

In summary, the knowledge of this study will contribute to refining and optimally implementing exoskeletons, with a focus on reducing fatigue and mitigating musculoskeletal risks, while considering the nuances of movement variability and cognitive resource allocation.

Furthermore, we would like to emphasize that the study also highlights the challenges, such as user discomfort and frustration, which can hinder the widespread adoption of this technology in real-world scenarios, especially for females.

The innovative focus lies on task and gender-specific variability including the muscle synergy approach. Analyzing muscle synergies can provide a nuanced understanding of muscle coordination and function, as well as the effects of interventions such as fatigue protocols or wearing an exoskeleton on these interactions.

Regarding the nature of this study protocol, we are aware that the potential outcomes we hypothesize are only speculative and need to be confirmed with the data we will collect. Moreover, with respect to the study design, there might be aspects of muscle fatigue and the interplay with cognitive resources that cannot be answered with this study design (e.g., what happens if different forms of additional cognitive tasks will be added or if we also integrate a mental fatigue protocol). Nevertheless, the described complex study design of this protocol will gain a lot of relevant insights to provide guidelines for optimizing the design of these robotic applications.

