Are there gender effects of using an upper body exoskeleton for both tasks regarding:Muscle synergies?Upper body posture?Cognitive resources?Comfort/discomfort, acceptance and usability?Are there gender effects of using an upper body exoskeleton for both tasks under previous physical fatigue for:Muscle synergy?Upper body posture?Cognitive resources?

The research questions will be answered using a randomized crossover study design (*cf.*
Figures 1, 2). Participants of each gender will be randomly assigned to different sequences of interventions, ensuring a balanced distribution of order effects. This design allows each participant to serve as their control, contributing to internal validity.

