### Eligibility criteria

Participants should be within the age range of 18–45 years, between 1.65 m and 2.05 m body height and do not have any chronic physical or mental health disorders.

The experiments will be executed by trained sports scientists with at least a Bachelor degree.

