#### Physical performance task (PILE task)

The PILE task, which was developed by Mayer et al. (45), is a functional assessment tool for measuring manual lifting ability. It involves lifting a weighted box in four movement cycles from a starting position to two predetermined heights: from the floor to hip height and from the hip to shoulder height. The task assesses cardiovascular endurance, overall lifting capacity, psychophysical fatigue of the trunk and limbs and motivational factors through repeated lifting cycles. During the task, the weight is increased after each successful cycle, starting at 4 kg for women and 6 kg for men. The total test duration is approximately 10–15 min. The aim is to assess lifting ability for specific heights, taking into account the maximum weight lifted, time to abort and heart rate at abort. The aim of the task is to calculate the work performed and the strength. The PILE task shows a high test–retest reliability with correlation coefficients of r = 0.87 for lifting at hip height and r = 0.93 for lifting at shoulder height (*p* < 0.001). Termination criteria include psychophysiological factors, aerobic capacity exceeding 85% of maximum heart rate, and safety concerns related to exceeding a predetermined weight limit. Normative values for test performance are calculated based on age, height and weight, with age influencing the calculation of aerobic capacity and height determining the tolerable lifting capacity. For this study purpose, we only use the hip to shoulder height task.

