### Sample size

The sample size was calculated on the outcome of muscle activity using G*power (*a priori*, ANOVA with repeated measures and interaction effect) with 2 groups (male/female), 2 tasks (Physical Performance Task, Precision Task), 2 conditions (with/without exoskeleton), and 2 fatigue protocols (with/without fatigue protocol) estimating an effect size of 0.25, an alpha error rate of 0.05 and a statistical power of 0.80, resulting in *N* = 36 participants for each group. With an estimated drop of 20% we will include a total of *N* = 80 (40 female/40 male) healthy participants with male and female participants equally.

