### Recruitment

Recruitment will take place through notices at the University of Hamburg as well via advertisements in local newspapers. By the use of a snowball concept, we will ask all participants to advertise the study and provide additional participants. In previous experiments, we have found that this strategy was particularly useful to find more participants.

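### The gender-by-fatigue fNIRS contrast is open to age confounding: the protocol names age as the possible modifier but neither balances it between women and men nor puts it in the stated model

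*Protocol article*

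**What the plan says.** All references are to the protocol article.

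- **Hypothesis (Discussion, Fatigue effects).** After fatigue, more executive control is expected to be needed. Of this mechanism the text says: "This mechanism should be equal for male and female participants and might only be affected by age (61". The test is by fNIRS: "This hypothesis will be proven by the analysis of the fNIRS data, regarding a potential shift from parietal to frontal cortex activation".
- **Who is eligible (Eligibility criteria).** "Participants should be within the age range of 18–45 years".
- **How they are found (Recruitment).** "Recruitment will take place through notices at the University of Hamburg as well via advertisements in local newspapers". In addition: "By the use of a snowball concept, we will ask all participants to advertise the study and provide additional participants". No age rule is given.
- **What is balanced (Sample size).** "40 female/40 male) healthy participants with male and female participants equally". This is the only recruitment quota.
- **What is randomised (end of the Introduction).** "Participants of each gender will be randomly assigned to different sequences of interventions, ensuring a balanced distribution of order effects". Randomisation concerns the order of conditions, not group membership.
- **What is recorded (Data management).** Age is among the personal data collected.
- **What is analysed (Statistical analysis).** fNIRS outcomes and the Borg scale each get a repeated-measures ANOVA. No age term is mentioned.

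**The concern.** Women and men are compared as they are recruited, so their comparability on anything other than gender depends on who volunteers. The protocol's own hypothesis is that gender should make no difference to the fatigue-related shift and that age might. That singles out age as the characteristic to keep apart from gender in this contrast.

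The crossover does not do this. Using each participant as their own control removes stable differences in level between people. It does not remove a characteristic that changes the size of a person's response to fatigue, which is the role the hypothesis gives to age. The gender-by-fatigue contrast compares within-person changes between two different sets of people. If those sets differ systematically in age, an age effect on the change can appear as a gender effect or hide one. Because the prediction is equality between genders, an unadjusted result in either direction would then be hard to interpret.

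**Working it through.** The protocol gives no figure for age spread, age gap or age slope, so there is nothing of its own to reproduce on this point. The inputs are as follows.

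- From the protocol: 36 per gender in the calculation, 40 per gender recruited, ages 18–45, alpha 0.05.
- Assumed: age SD 5 to 7.8 years, where 7.8 = 27/√12 is the SD if ages are uniform on 18–45; systematic age gap 2 to 8 years; correlation between age and the within-person fatigue response 0.1 to 0.5.

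**Step 1: imbalance by chance alone.** The standard error of the difference in mean age is SD × √(2/n). With n = 36:

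- SD 5: 5 × 0.2357 = 1.18 years; 95% range ±1.96 × 1.18 = ±2.3 years.
- SD 7.8: 7.8 × 0.2357 = 1.84 years; 95% range ±3.6 years.

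These figures describe what independent sampling would produce. They are not bias. Variation due to age is part of the residual variance, so over repeated samples an unadjusted test still rejects in about 5% of trials when neither gender nor a systematic age gap is at work.

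**Step 2: a systematic gap.** If recruitment produces a real age gap, the bias in the gender contrast in SD units is d = correlation × gap / age SD. With 36 per group, the type I error follows from the noncentral t distribution with 70 degrees of freedom and noncentrality d × √(36/2). For age SD 7.8 and no true gender effect:

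| Correlation | Gap 2 y | Gap 3.4 y | Gap 5 y | Gap 8 y |
|---|---|---|---|---|
| 0.1 | 5.1% | 5.4% | 5.8% | 7.1% |
| 0.3 | 6.2% | 8.5% | 12.7% | 25% |
| 0.5 | 8.4% | 15% | 27% | 57% |

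For example, correlation 0.3 and gap 5 years give d = 0.3 × 5 / 7.8 = 0.19, noncentrality 0.19 × 4.24 = 0.82, and a rejection rate of 12.7%. The effect is trivial when gap and correlation are both small, and material when both are moderate.

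**Step 3: the price of adjusting.** With age in the model, the variance of the gender contrast is multiplied by 1/(1 − r²), where r is the correlation between age and gender. For equal groups this equals 1 + (gap / (2 × SD))². At SD 7.8 it is 1.05 for a gap of 3.4 years, 1.10 for 5 years and 1.26 for 8 years. With similar age distributions it is close to 1, so the sample size is practically unchanged.

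**Step 4: which contrasts are exposed.** Exoskeleton and fatigue effects pooled over gender are within-person, and age cannot confound them. A main effect of age on the fNIRS level cancels in each person's fatigue change. The exposed quantity is the difference between genders in that change, and the term that protects it is age-by-fatigue.

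**The case against.** Several counter-arguments are sound and limit the point.

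- **Research question 2c.** A reader might infer that 2c itself is confounded. As worded in the Introduction, it asks about gender effects of using the exoskeleton under prior fatigue, which is gender by exoskeleton within the fatigued state. If age alters the fatigue response equally with and without the device, that alteration cancels. Confounding 2c would need age to modify the exoskeleton effect, which the protocol does not suggest. The exposure is mainly the gender-by-fatigue hypothesis in the Discussion.
- **No gap is shown.** The same notices, newspapers and referrals reach both genders. That one source brings younger people, or that referral chains load one gender, is supposition.
- **The sentence is hedged.** The text says that age might matter, and the protocol calls its hypotheses speculative. The 18–45 limit also bounds the age spread.
- **Lifting task.** A reader might take "with age influencing the calculation of aerobic capacity and height determining the tolerable lifting capacity" as further evidence. That phrase concerns test norms and aerobic capacity in the PILE task and says nothing about fNIRS.
- **Covariates may be set elsewhere.** A fuller analysis plan could add age. This weakens any complaint of omission. It does not alter the fact that the recruitment described balances gender only, or that the model as stated has no age term.

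What survives is narrow: a non-randomised contrast, a modifier that the protocol itself names, and a stated model that does not use a variable already collected.

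**Conclusion.** The point holds as a low-cost improvement, not as an error or contradiction in the plan. It concerns one contrast, the gender difference in the fatigue-related fNIRS shift, and matters only if recruitment produces a systematic age difference between women and men and age affects that shift. The protocol establishes neither. Under the stated assumptions the nominal 5% becomes anything from 5.1% (correlation 0.1, gap 2 years) to 57% (correlation 0.5, gap 8 years); at correlation 0.3 it is 8.5% for 3.4 years and 12.7% for 5 years. These rates are conditional on a fixed systematic gap. The chance ranges of ±2.3 to ±3.6 years are not evidence of bias.

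A reader might also infer that the trial cannot separate age from gender at all. That goes too far: age is recorded, and adjustment is possible as long as the age distributions overlap.

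**What to change.** In Statistical analysis, add centred age and its interaction with fatigue to the model for the fNIRS gender contrasts, and report age by gender. The interaction is the essential part, because age as a main effect alone leaves the gender-by-fatigue contrast unadjusted.

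In Recruitment, where feasible, monitor the age distributions of women and men as they accrue and direct the remaining recruitment to keep them similar. A fixed age split or a cap on referrals is not needed.

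The cost is one or two degrees of freedom, no new data, and some attention to the recruitment log. Keeping the ages similar also limits the loss of precision shown in step 3, which adjustment alone cannot avoid.

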### Possible pitfalls and limitations

Most pitfalls in exoskeleton research occur due to limitations of the device. Either, the exoskeleton is a research prototype, which makes it oftentimes prone to failure. Or in commercially available (and therefore more robust) exoskeletons, their applicability for certain tasks are limited, placing constraints on support torque modifications for a heterogenous pool of test subjects or remain difficult to fit to certain test subjects (often times women due to differences in body shape in comparison to men).

In order to avoid these pitfalls, we intend to use the commercially available exoskeleton exoIQ S700. It is specifically designed to provide support in the task being assessed (overhead work) with numerous torque support adjustments. Moreover, its comparatively wide range of size adjustments (shoulder width, back length, arm length) and textiles, that are designed to fit both genders, should suffice to significantly mitigate these possible issues.
